#### Data collection for the content validation

Content validation will be performed to assess the clinical relevance and the representativeness of the practice of interprofessional teams in post-operative cardiac surgery setting of the items of the extraction tool. Content validation will follow two steps [46]. First, an expert committee will be recruited from clinicians, managers, and researchers who have expertise in postoperative cardiac surgery. The identification and recruitment of experts will be conducted by our research team and will include experts in Canada. A total of 10 experts will be recruited, including at least the following five: 1) an ACNP who worked a minimum of one year within a postoperative cardiac surgery unit outside of our associated UHC, 2) a cardiac surgeon or fellow in cardiac surgery who worked at least two years in an acute care centre outside of our associated UHC, 3) a nurse manager who has led for at least one year, a postoperative cardiac surgery unit, within our associated UHC, 4) a healthcare professional who worked in the data warehouse of our associated UHC for at least one year, and 5) a researcher in nursing or healthcare sciences with an expertise in measurement instruments and/or cardiac surgery.

Second, an electronic survey [47] will be created and sent to each expert of the committee. The survey will be composed of all items of the extraction tool (best-practice guidelines and confounding variables). For each item, experts will assess its relevance using a 5-points Likert scale [48, 49]. Additional spaces for qualitative comments and suggestions will be included in the survey. Two rounds of revision are planned. After the first round, our team will update the extraction tool and revise any unclear items based on the experts’ recommendations, and an updated version will be resubmitted to the expert committee.

#### Data collection for the criterion validation

The criterion validation of the extraction tool will follow two consecutive steps. Firstly, the best-practice guidelines of The Society of Thoracic Surgeons (STS) have been selected as the gold standard of comparison for this study. For many years, the STS has been a leading healthcare organization in the development and validation of best-practice guidelines and performance measures in the care of patients in cardiac surgery settings [10]. In 2007, the STS developed and validated 21 performance measures for the delivery of high quality of care for patients who underwent CABG, valve repair, and CABG/valve repairs [50, 51]. For this project, five performance measures were selected, including: 1) prolonged mechanical ventilation higher than 24 hours in the ICU; 2) a 30-day readmission rate at the postoperative cardiac surgery unit after hospital discharge; and prescription of the 3) anti-platelet, 4) beta blocker, 5) and lipid-lowering agent, during the hospitalization at the postoperative cardiac surgery unit and at discharge. Each performance measure is operationalized as the proportion of patients who achieved the outcome (e.g., proportion of patients who were under prolonged mechanical ventilation) over the total sample size [46, 47].

Secondly, 30 patient health records will be reviewed independently by two reviewers on two occasions, including the first author and a research assistant. For the first round of revision, the patient’s health record will be reviewed with the extraction tool. For the second round of revision, the records will be reviewed with the five performance measures from the STS.

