### Data collection

An extraction tool will be developed and pilot-tested, based on the best-practice guidelines and the confounding variables related to the patient and interprofessional team characteristics (Fig 1). One extraction will be completed per patient per day during the hospitalization in the postoperative cardiac surgery unit, by the first author or a research assistant. The development of the extraction tool followed the Consensus-based Standards for the selection of health measurement instrument (COSMIN) guidelines [46] and will include three stages: the content validation; the criterion validation; and the pilot-test.

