### Data analysis

Statistical analysis will be conducted to meet objectives one, two and three. The unit of observation will be the patient-level and the unit of analysis will be the interprofessional team with or without ACNP-level.

#### Objective 1

For the content validation [56, 57], a Fleiss Kappa will be calculated for each round of revision and a value between 0.60 and 0.80 will be targeted [48, 49]. The content validity index (CVI) of each individual item of the extraction tool will be calculated from the proportion of experts who rated a score of 4 or 5 on the Likert scale [58]. A CVI of 0.80 will be targeted for each item and items with a value below 0.80 will be removed or modified. Then, the proportion of items with a CVI value above 0.80 will be calculated to determine the overall CVI of the extraction tool. A value higher than 0.80 for the overall CVI of the extraction tool will be targeted [46]. Qualitative comments and recommendations by experts will be analyzed by content analysis [59].

For the criterion validation, Spearman correlation will be calculated to assess the correlation between the measures of the gold standard (e.g., the performance measures of the STS), and the measures of the extraction tool. Values of Spearman correlation higher than 0.70 will be targeted [48, 49].

#### Objective 2

Descriptive analysis will be performed to assess the level of adherence by interprofessional teams with and without ACNPs, as well as the confounding variables for patients under the care of both teams [60]. A graphic illustration will be created to visualize the tendency and distribution of the level of adherence to best-practice guidelines by interprofessional teams with and without ACNPs. An analysis of missing data will be conducted to examine the quality and distribution of missing data within patient health records and electronic databases. Team meetings and consultations with clinicians and statisticians will be held to discuss and identify potential causes of missing data, as well as to conduct a statistical analysis to manage them [61]. Bivariate analysis will be conducted, and the statistical significance will be based on a *p*-value of 0.05 [60]. The Bonferroni correction will be applied for the examination of each confounding variable related to the patient and interprofessional teams’ characteristics [62].

#### Objective 3

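### The criterion validation is largely circular and weakly informative: its gold standard consists of the tool's own items, and the unit of the Spearman correlation is not stated

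*Protocol article*

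**What the plan says.** Under Data collection for the criterion validation, the STS guidelines are named the gold standard: "For this project, five performance measures were selected". They are prolonged ventilation beyond 24 hours, 30-day readmission, and prescription of an anti-platelet, a beta blocker and a lipid-lowering agent. Their form is fixed there too: "Each performance measure is operationalized as the proportion of patients who achieved the outcome", with the total sample as denominator.

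The same section sets the procedure: "30 patient health records will be reviewed independently by two reviewers on two occasions, including the first author and a research assistant". The two occasions are then separated: "For the first round of revision, the patient’s health record will be reviewed with the extraction tool", and "For the second round of revision, the records will be reviewed with the five performance measures from the STS".

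Under Data analysis, Objective 1, "Spearman correlation will be calculated to assess the correlation between the measures of the gold standard" and those of the tool, and "Values of Spearman correlation higher than 0.70 will be targeted". The unit over which the correlation is computed is not given.

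The tool itself is built, under Data collection, "based on the best-practice guidelines and the confounding variables related to the patient and interprofessional team characteristics".

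**The concern.** There are three difficulties.

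1. **The statistic.** Each gold-standard measure is one number for the whole sample. If the tool yields five matching numbers, Spearman's coefficient rests on five pairs. Two of the measures are adverse events and three are prescriptions, so their frequencies probably differ widely. The ranking would then follow from base rates, whatever happens record by record.
2. **The criterion.** The five measures are also contents of the tool, taken from the same charts by the same two people. A high coefficient would mainly show that the same items can be abstracted twice with similar results.
3. **The coverage.** The dependent variable in Objective 3 is the average composite of 12 guidelines, and most of that composite is never compared with anything.

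At stake is what may be claimed for the tool. The Discussion offers it to cardiac surgery research and beyond, and Objective 3 uses its composite as the outcome. The regression can still be run, but a criterion-validity statement would carry less than it appears to.

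**Working it through.** The 0.70 target and the 30 records are stated without derivation, so there is no plan figure to reproduce. The check asks what a value above 0.70 would show.

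**Inputs from the protocol:** 30 records, five measures, target above 0.70, 12 scored guidelines. **Assumption:** the base rates, because the protocol gives none; several sets are used.

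**Step 1. Overlap and coverage.**

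| STS measure | Place in the tool | In the adherence score? |
|---|---|---|
| Anti-platelet | Pharmacotherapy guideline | Yes |
| Beta blocker | Pharmacotherapy guideline | Yes |
| Lipid-lowering agent | Pharmacotherapy guideline | Yes |
| Ventilation over 24 h | Patient variable, same cut-off | No |
| 30-day readmission | Patient variable | No |

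Guidelines without a comparator: 12 − 3 = 9 (anticoagulants, four laboratory tests, four assessments). The composite has none either.

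**Step 2. Five proportions: why patient-level error is invisible.** A proportion depends only on the total. Suppose the STS read finds 27 of 30 patients on a drug, and the tool also finds 27 but misses a different three. Both proportions are 27/30 = 0.90. Observed agreement is 24/30 = 0.80. Chance agreement is 0.90² + 0.10² = 0.82. Kappa = (0.80 − 0.82)/(1 − 0.82) = −0.11. In general, shuffling the tool's values across patients leaves every proportion unchanged: in simulation rho was 1.00 in every run, with mean kappa 0.00.

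**Step 3. Five proportions: chance-only agreement.** The two reads are drawn independently as binomial(30, p)/30 for each measure, and rho is computed over the five pairs. Rates are in the order ventilation, readmission, anti-platelet, beta blocker, lipid-lowering agent.

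| Assumed rates (%) | P(rho > 0.70) |
|---|---|
| 8, 12, 95, 85, 90 | 0.87 (median rho about 0.89) |
| 5, 10, 95, 85, 90 | 0.87 |
| 10, 15, 90, 80, 70 | 0.95 |
| 20, 30, 60, 70, 80 | about 0.91 |
| 8, 12, 90, 90, 90 | about 0.66 |
| 30, 40, 50, 60, 70 | about 0.69 |
| all 50 | about 0.09 |

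For reference, with unrelated ranks and no ties, 8 of the 120 orderings of five ranks exceed 0.70 (1 at 1.0, 4 at 0.9, 3 at 0.8): 8/120 = 0.067.

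**Step 4. Five proportions: random extraction error.** Error is added to the tool read only, using the second, third and fourth rate sets.

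| Random error | P(rho > 0.70) | Mean kappa |
|---|---|---|
| 20% | 0.83–0.91 | 0.30–0.53 |
| 35% | 0.49–0.67 | 0.12–0.24 |

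**Step 5. Over patients, per item.** On two binary variables Spearman's coefficient equals phi. In the same simulations, P(phi > 0.70) per item is 0.34–0.98 with 5% error and 0.01–0.26 with 20% error, so the check responds to error. It is imprecise, however. With z = atanh(0.70) = 0.867:

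- Variance 1.06/(n − 3): SE = √(1.06/27) = 0.198; interval tanh(0.867 ± 1.96 × 0.198) = 0.45 to 0.85.
- Variance (1 + 0.70²/2)/(n − 3): SE = √(1.245/27) = 0.215; interval 0.42 to 0.86.

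For items at 5% or 95%, phi was undefined in about 20–24% of samples of 30.

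**The case against.** The strongest reply is that the five-point reading is not what the analysis section says. It speaks of correlation values in the plural and opens by naming the patient as the unit of observation. One coefficient per measure across 30 patients fits that wording at least as well. This stands: the unit is open, and on the patient-level reading the check can fail. It does not remove the point, because the criterion section defines the measures as sample proportions, and neither the overlap nor the coverage depends on the unit.

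A reader might infer that the check cannot fail, or that the tool would be declared valid whatever its accuracy. The protocol does not support that. Even over five proportions, 35% random error fails the target in a third to a half of runs, and the pass rate under chance agreement depends on assumed base rates.

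A reader might also infer that this is pure test–retest and says nothing about validity. That is too strong for the drug items. The tool scores each guideline from 0 to 2 per day, and drug adherence requires daily prescription plus monitoring; the STS measure is prescription during the stay and at discharge. Two different operationalisations of one construct give some concurrent evidence, though limited.

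Finally, Objective 1 has other safeguards: item-level content validity indices, and kappa above 0.60 targeted on 30 pilot records and again on 30 cohort records. The 0.70 is a target, not a condition for Objective 3, and nowhere is criterion validity claimed for the composite. All this is true and limits the damage. But content relevance and inter-rater reliability are not agreement with a criterion.

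**Conclusion.** The point holds in a limited form: the criterion validation is largely circular and only weakly informative. If run over five proportions, it passes in about 66–95% of simulated runs with no more than chance agreement per patient, provided base rates differ as assumed, and in about 9% if they are all equal. If run over patients, it can detect error, but a coefficient of 0.70 on 30 records is compatible with anything from about 0.42–0.45 to 0.85–0.86.

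Three facts rest on the text alone. All five criterion items are tool items; they come from the same charts and the same two people with no stated blinding between rounds; and only three of the 12 scored guidelines are compared. The result would give limited concurrent evidence for those three and none for the other nine or the composite. This should be corrected, but it does not stop the main regression.

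**What to change.** Replace the Spearman target by patient-level agreement for each of the five shared items, against the STS definition: kappa, sensitivity and specificity, with 95% confidence intervals and the raw 2×2 counts. Compare like with like: for the drug items, use the tool's prescription component, not the full 0–2 score.

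Keep the double reading, and compare one person's tool read with the other person's STS read of the same record. The planned two readers on two occasions already allow this if both read every record.

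For the adherence score, limit the criterion-validity claim to the three drug items. State that the other nine guidelines and the composite rest on content validity and inter-rater reliability.

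The cost is a narrower claim; no records or staff are added. The same charts remain the only source, so some dependence stays. Estimates for rare or near-universal items will be imprecise or undefined. At an assumed 95% prescription rate, specificity rests on 30 × 0.05 = 1.5 patients on average, and on none in 0.95³⁰ = 21% of samples. At an assumed 8% event rate, sensitivity rests on 30 × 0.08 = 2.4. The counts and intervals would show this openly, which a single threshold does not.

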#### Data collection for the pilot-test

A pilot-test will be conducted to assess the feasibility of using the tool, standardize data collection among reviewers, examine the quality and accessibility of the retrospective data, and update the tool if needed. Four iterative steps will be included in the pilot-test [52–55]. First, two reviewers will conduct the pilot-test and data collection. Training sessions and documentation will be given to the reviewers.

Secondly, 30 patient health records from hospitalized patients in the postoperative cardiac surgery unit between January 1, 2019, and January 31, 2020, will be randomly selected. These patients will not be included in the retrospective cohort. Data will be collected by the two reviewers with the extraction tool. Inter-rater reliability will be assessed and a Cohen kappa higher than 0.60 will be targeted [55].

Thirdly, a triangulation of the available data will be performed to assess the quality and accessibility of the data. Multiple data sources will be screened between the electronic databases and patient health records. Items from the extraction tool with a high quantity of missing data or low quality of available data will be modified or removed.

Finally, frequent meetings among all research team members will be conducted to discuss divergences, reinforce convergences, and establish a consensus. The extraction tool will be updated after the pilot-test if needed [52].

A calibration session among the reviewers will be conducted during the data collection from the main retrospective cohort. A total of 30 patient health records will be reviewed by two independent reviewers [49, 50]. Inter-rater reliability will be assessed and a Cohen Kappa value higher than 0.60 will be targeted [55].

### Data analysis

Statistical analysis will be conducted to meet objectives one, two and three. The unit of observation will be the patient-level and the unit of analysis will be the interprofessional team with or without ACNP-level.

#### Objective 1

For the content validation [56, 57], a Fleiss Kappa will be calculated for each round of revision and a value between 0.60 and 0.80 will be targeted [48, 49]. The content validity index (CVI) of each individual item of the extraction tool will be calculated from the proportion of experts who rated a score of 4 or 5 on the Likert scale [58]. A CVI of 0.80 will be targeted for each item and items with a value below 0.80 will be removed or modified. Then, the proportion of items with a CVI value above 0.80 will be calculated to determine the overall CVI of the extraction tool. A value higher than 0.80 for the overall CVI of the extraction tool will be targeted [46]. Qualitative comments and recommendations by experts will be analyzed by content analysis [59].

For the criterion validation, Spearman correlation will be calculated to assess the correlation between the measures of the gold standard (e.g., the performance measures of the STS), and the measures of the extraction tool. Values of Spearman correlation higher than 0.70 will be targeted [48, 49].

#### Objective 2

Descriptive analysis will be performed to assess the level of adherence by interprofessional teams with and without ACNPs, as well as the confounding variables for patients under the care of both teams [60]. A graphic illustration will be created to visualize the tendency and distribution of the level of adherence to best-practice guidelines by interprofessional teams with and without ACNPs. An analysis of missing data will be conducted to examine the quality and distribution of missing data within patient health records and electronic databases. Team meetings and consultations with clinicians and statisticians will be held to discuss and identify potential causes of missing data, as well as to conduct a statistical analysis to manage them [61]. Bivariate analysis will be conducted, and the statistical significance will be based on a *p*-value of 0.05 [60]. The Bonferroni correction will be applied for the examination of each confounding variable related to the patient and interprofessional teams’ characteristics [62].

#### Objective 3

A multivariate linear regression model will be developed to examine the association between interprofessional teams with and without ACNPs and the level of adherence to best-practice guidelines [63–65]. An examination of the distribution of the data will be performed. In the case of an abnormal distribution of the data, a transformation will be conducted to adjust the statistical model based on the observed data. The independent variables will include the interprofessional teams with and without ACNPs, as well confounding variables. A correlation matrix will be developed, and tolerance value lower than 0.2 and a variance inflation factor (VIF) value higher than 5 will be used to identify multicollinearity between independent variables [63–65]. Independent variables with multicollinearity will be removed one at the time and a new regression will be calculated. The dependent variable of the regression model will be the average composite score (%) of the level of adherence to best-practice guidelines. Statistical significance will be based on a *p*-value of 0.05. Sensitivity analysis will be conducted based on a selection of confounding variables related to the characteristics of the patient (e.g., length of stay, ICU readmission). The selection of these confounding variables will be based on the observed data and descriptive analysis. The residual analysis and the analysis of the R^2^ will be conducted to assess the goodness-of-fit of the multivariate linear regression model.

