### Study setting

This study will be conducted at a UHC in Québec, Canada, where approximately 1,000 cardiac surgeries are performed annually in a 36-bed postoperative cardiac surgery unit.

After cardiac surgery, patients are admitted to the intensive care unit (ICU), and are under the care of ICU teams. At the time of data collection, the ICU teams in Québec, Canada did not include ACNPs. On average, patients are hospitalized for 24 hours in the ICU before being transferred to the postoperative cardiac surgery unit. Patients readmitted to the ICU are under the care of ICU teams.

Upon admission to the postoperative cardiac surgery unit, patients are assigned to the care of interprofessional teams with or without ACNPs. Team assignment depends on the current workload of each team, and the availability of the beds in the unit. Interprofessional teams with ACNPs are responsible for 16 of the unit’s beds (44%) and interprofessional teams without ACNP are assigned 20 of the unit’s beds (56%). Patients are followed by their respective teams from their admission to the cardiac surgery unit until hospital discharge or death. On average, the length of stay at the hospital after the surgery ranges from 9 to 11 days [33].

Interprofessional teams with and without ACNPs include the following: cardiac surgeons and physician residents, nursing teams, skin and wound care specialists, physiotherapists, nutritionists, respiratory therapists, social workers, and other medical specialists. Interprofessional teams with and without ACNPs ensure daily follow-up of patients, assessment of the patient’s clinical and psychosocial condition, management of pharmacotherapy, clinical interventions, prescribing and monitoring of laboratory tests, lifestyle promotion, and the preparation of patients for hospital discharge.

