### The practice of acute care nurse practitioners in the postoperative cardiac surgery unit

Since 2017, seven ACNPs practice in postoperative cardiac surgery, based on a monthly rotation system. Two ACNPs simultaneously practice within interprofessional teams and collaborate with other clinicians to ensure the daily follow-up of the patients after cardiac surgery. In addition to the activities described above, the ACNPs also teache coping strategies, lifestyle promotion, cardiac rehabilitation, preparation of the patients and families for the in-home recovery after discharge. The ACNPs support the preparation for hospital discharge (e.g., prescription of the patient medication after discharge, summary for the family physician, etc.) [34].

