#### Independent variable: Interprofessional teams with and without acute care nurse practitioners

A dichotomous variable will be created to measure the inclusion of at least one ACNP within the interprofessional team. For patients under the care of an interprofessional team with ACNPs, an additional descriptive variable will measure the number of days where the ACNP was involved in the daily follow-up of the patient, on the entire hospitalization at the postoperative cardiac surgery unit.

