Secondly, an overall composite score will be calculated from the sum of all the scores of all best-practice guidelines (n = 12), ranging from zero to 24. The overall composite score will be transformed into a value in percentage ranging from 0 to 100% (i.e., composite score/24 * 100), such that 100% represents a complete adherence (24/24). An increase of the score will be associated with an increase of the level of adherence to best-practice guidelines by interprofessional teams. An overall score will be calculated per patient per each day hospitalized in the postoperative cardiac surgery unit.

Finally, an average composite score will be calculated from the average of all overall scores during the patient’s hospitalization at the postoperative cardiac surgery unit. An average composite score will be calculated for all patients included in the retrospective cohort.

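### The plan names the team as the unit of analysis but sizes and fits a patient-level regression with no allowance for correlation among patients of the same team

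*Protocol article*

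**What the plan says.** The opening of Data analysis sets two levels: observation is by patient, but "the unit of analysis will be the interprofessional team with or without ACNP-level".

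Objective 3 in the same section then gives the model: "A multivariate linear regression model will be developed to examine the association between interprofessional teams with and without ACNPs and the level of adherence". Its outcome is the average composite score, which the section on the dependent variable defines per patient: "An average composite score will be calculated for all patients included in the retrospective cohort". Study population and sample gives a minimum of 183 patients for one such regression (f² = 0.15, power 0.80, 5%) and raises it to 300, as 150 matched pairs. None of these places names a random effect, a clustered or robust variance, or a design effect.

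Exposure is defined at team level: "A dichotomous variable will be created to measure the inclusion of at least one ACNP within the interprofessional team". Under Study setting, "Team assignment depends on the current workload of each team, and the availability of the beds in the unit", and each patient then stays with that team until discharge or death. On the ACNP side, "seven ACNPs practice in postoperative cardiac surgery, based on a monthly rotation system", two of them at a time. The number of distinct teams on either side is not stated. The only provider code listed is the cardiac surgeon's.

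**The concern.** The stated unit and the stated model do not match. A team-level analysis has as many data points as there are teams, whereas the sample size and Objective 3 count patients. An analyst cannot follow both.

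The mismatch affects the inference. The adherence score records what a team does: prescribing, monitoring, daily assessment and follow-up action. Patients cared for by the same team, in the same period, share the same few clinicians and habits, so their scores are likely to be correlated. Every patient of a team has the same exposure value, so that correlation adds directly to the variance of the with/without-ACNP contrast. A regression that treats the patients as independent leaves this variance out. The consequence would be confidence intervals that are too narrow and a test of H1 that rejects too often at p < 0.05.

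**Working it through.** **The plan's own figure.** A standard multiple-regression calculation (noncentral F, λ = f² × N, 14 predictors, f² = 0.15, alpha 0.05, power 0.80) gives N = 135. The stated 183 is not reproduced from the stated inputs; at 183 the power would be 0.93. That is a separate matter. What counts here is that 183 is a number of patients with no stated clustering allowance.

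**Inputs for the clustering check**
- N = 300 patients, 150 per side (Study population and sample).
- Nominal two-sided 5% test. The article states 0.05 but not sidedness, so two-sided is assumed.
- Number of clusters K: not given. One scenario takes team-months: 1 January 2019 to 31 January 2020 is 13 months, and 13 × 2 sides = 26. This is an assumption, because monthly rotation is stated for the ACNPs only. K = 2, 4 and 6 are shown as alternatives.
- ICC: not given; range 0.01 to 0.10 assumed.

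**Formulas.** m = N/K; design effect DE = 1 + (m − 1) × ICC; true SE ÷ naive SE = √DE; effective n = N/DE; actual type I error = 2 × [1 − Φ(1.96/√DE)].

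**26 clusters:** m = 300/26 = 11.54.

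| ICC | DE | true SE ÷ naive SE | effective n | type I error |
|---|---|---|---|---|
| 0.01 | 1.11 | 1.05 | 271 | 6.2% |
| 0.02 | 1.21 | 1.10 | 248 | 7.5% |
| 0.05 | 1.53 | 1.24 | 196 | 11.3% |
| 0.10 | 2.05 | 1.43 | 146 | 17.1% |

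At ICC 0.05 the true SE is 24% larger than the naive one. Equivalently, the naive SE is understated by 1 − 1/1.24 = 19%.

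**Fewer clusters**

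| K | type I error, ICC 0.01 | effective n | type I error, ICC 0.05 | effective n |
|---|---|---|---|---|
| 6 | 11% | 201 | 29% | 87 |
| 4 | 14% | 172 | 37% | 64 |
| 2 | 21% | 120 | 50% | 36 |

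**Simulation** (4,000 runs per cell, no ACNP effect, ordinary two-group test). With 26 clusters of 11 patients, rejection rates were 6.0%, 7.7%, 10.0% and 16.6% at ICC 0.01, 0.02, 0.05 and 0.10. At ICC 0.05 they were 28.9% with 6 clusters, 36.3% with 4 and 50.8% with 2. These agree closely with the formula.

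**Possible offsets**
- *Surgeon in the model.* If surgeons work across both sides, surgeon clustering does not inflate the error (simulated 4.5% to 5.0% with 8 surgeons assumed). Adjusting for surgeon removes surgeon variation only and leaves team and rotation variation in the residual.
- *Ignoring the 1:1 matching.* This acts the other way: simulated error is 4.2% at pair correlation 0.05 and 2.7% at 0.20. Age, sex and type of surgery are also measured as confounders, so little pair correlation should remain after adjustment. It cannot be relied on to cancel a team effect.

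**The case against.** The strongest reply is that the article never says the errors are independent. It names a linear regression without a variance estimator, and clustered standard errors can accompany that model. A condensed article may leave the choice to an analysis plan that is not shown. This stands in part: a reader might infer that the published p-values will certainly be too small, and the documents do not go that far. The reply does not remove the conflict over the unit of analysis, which is in the text and which an analysis plan would have to override. Nor does it explain a patient count with no stated clustering allowance.

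The reply on cluster structure also has force. The 26 team-months are not in the protocol. Nothing says that the teams without ACNPs change monthly, and with hospital stays averaging 9 to 11 days some patients straddle two months. A reader might equally infer that a team-level analysis has exactly two observations. The documents do not settle this: Study setting speaks of teams in the plural on each side, and no count is given.

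Finally, at ICC 0.05 with 26 clusters the effective n of 196 still exceeds the stated minimum of 183. That answers a worry about power in that scenario. It does not answer the inflated error rate, which arises from the standard error whatever the sample size.

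**Conclusion.** The conflict is established by the text: a team-level unit of analysis is declared, and a patient-level sample size and model are specified. If that model is run as an ordinary regression, its standard error for the ACNP contrast is too small under any positive within-team correlation, because exposure is constant within a team.

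The direction needs only that correlation to be positive, which the outcome and the care arrangement make likely but which no figure in the protocol quantifies. The size depends on two numbers that the documents do not give. With 26 assumed clusters, the actual type I error runs from about 6% to 17% over ICC 0.01 to 0.10. It is higher with fewer clusters, reaching about 21% at ICC 0.01 with one team per side. None of these figures should be read as the error rate of this study.

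With one team per side, the lasting difference between the two teams and the effect of having an ACNP are the same contrast. A team-by-month term would then leave the main problem untouched and could give false reassurance.

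**What to change.** 1. Reconcile the opening of Data analysis with Objective 3 and the sample-size paragraph: the patient is the unit of analysis, and the team is the level at which exposure is defined.
2. State how many distinct teams there are on each side and what the clustering unit is.
3. Record a team and rotation-period identifier at extraction. The listed variables cover with/without ACNP, ACNP days and surgeon, so it should not be assumed that this field is already collected.
4. Where there are enough clusters, fit the primary model with a random intercept for the cluster, or with cluster-robust errors, using a small-sample correction (for example Kenward-Roger or CR2). Keep surgeon in the model.
5. In either case, limit the conclusion to the team arrangements in this one unit. If there is one team per side, say that the team and ACNP effects cannot be separated and that no cluster correction resolves this.

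The cost is a wording change, one added extraction field, one model option and somewhat wider confidence intervals.
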